## Results

Recruitment for the trial commenced in May 2020 and concluded in November 2023. The study is closed as of September 2024 due to slow recruitment. A total of 34 participants were recruited. Data analysis is being performed in 2025, and the study results are expected to be published in late 2025.

## Discussion

### Principal Findings

PRP has emerged as a novel treatment for the management of a variety of dermatological conditions, including LS, because of its regenerative properties and potential to alleviate symptom burden [14]. To date, a number of studies have been conducted investigating PRP as a treatment for LS; however, these have been either case series or uncontrolled studies or studies that used multiple interventions such as both PRP and adipose-derived stem cells, limiting the ability to differentiate the efficacy of individual interventions [13]. Franic et al [21] highlighted significant symptom improvement in a premenopausal woman treated with PRP, underscoring its potential as a therapeutic alternative in cases resistant to conventional treatment methods.

Despite these limitations, these studies have reported encouraging results in terms of symptom relief for patients with LS, reducing itching, pain, and discomfort [26] but lack adequate power, standardized protocols, and comparison to a control. Other gynecological studies have reported a beneficial effect of PRP in patients with stress urinary incontinence, pelvic organ prolapse, genitourinary syndrome of menopause, vaginal fistula, and LS; however, these studies have the same limitations as described above [20,27].

This study was designed as a randomized controlled trial to fill the gap in existing literature about the efficacy of PRP for the treatment of vulvar LS. It aims to provide other researchers in this field with a standardized protocol, including methods of preparation and injection of PRP and the use of validated outcome measures assessing both the clinical signs of disease and subjective effects of the disease on the quality of life.

### Limitations

As a study protocol, there are several anticipated limitations to consider. This trial is being conducted at a single private clinical center, which may limit the generalizability of findings to other settings, particularly public hospitals or international populations. Although the study is powered to detect a significant difference between groups, the modest sample size may not capture rare adverse events or allow detailed subgroup analysis. Additionally, although outcome assessors and participants are blinded, the treating investigator must remain unblinded for procedural reasons, introducing a potential risk of bias. Lastly, although validated tools such as the clinical scoring system for LS and quality of life measures are employed, patient-reported outcomes are inherently subjective and may be influenced by expectations, even in a placebo-controlled setting.

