Platelet-rich plasma (PRP) is an autologous platelet concentrate, which contains the platelet-derived growth factor, transforming growth factor, and epidermal growth factor, and it is hypothesized to promote wound healing and tissue regeneration [13,14]. It has yielded positive results in orthopedic, reconstructive surgery, dentistry, dermatology, and musculoskeletal medicine [15-18]. PRP has been studied as a treatment for LS [19], but issues with small sample sizes, heterogenous study methodologies, short-term follow-up, and the use of unvalidated outcome measures are the limitations that have prevented the recommendation of PRP use in clinical practice [13]. In the context of LS, PRP may exert therapeutic effects through its anti-inflammatory and immunomodulatory properties. Growth factors such as transforming growth factor-β and platelet-derived growth factor found in PRP can modulate the immune responses and promote tissue remodeling. These effects may reduce local inflammation, improve dermal regeneration, and help restore the structural integrity of vulvar tissues affected by LS. Therefore, this trial has been designed as an adequately powered, placebo-controlled randomized study to evaluate the safety and efficacy of PRP in LS by using validated outcome measures.

In contrast to prior studies [20,21], this trial addresses these limitations by employing a randomized, double-blind, placebo-controlled design with an adequately powered sample size. It also utilizes validated clinical and patient-reported outcome measures, including the clinical scoring system for LS, Dermatology Life Quality Index, and Australian Pelvic Floor Questionnaire, with a planned 12-month follow-up. These methodological strengths are designed to provide robust evidence on the efficacy and safety of PRP for LS.

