#### Sample Size and Power Calculations

Sample size calculations are based on the pilot study on 28 patients [20], in which 80% of the participants treated with PRP experienced an improvement in their symptoms. Assuming a difference of 30% between PRP and normal saline at 12 months, an α risk of 5%, and a power of 80%, a sample size of 31 participants for each group is required. Assuming that 10% of the participants withdraw or are lost to follow-up, a sample size of 34 participants for each group is required or a sample size of 68. The pilot study used subjective symptom improvement as its primary outcome, whereas this trial’s primary outcome is the LS clinical score, an objective physician-rated measure. Although these outcomes differ, symptom improvement in the pilot study was used as a surrogate to estimate a conservative effect size for this study, given the lack of prior data on LS clinical score changes with PRP. This study will also evaluate secondary outcomes, including subjective symptom scores, allowing for comparisons between subjective and objective measures.

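### The article still calls the trial powered after closing at 34 of 68 participants; on its planning effect, power at 34 is about 45% (two-sided) to 58% (one-sided)

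*Protocol article*

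**What the plan says.** Two places in the protocol article describe the trial as powered. The Limitations section of the Discussion says "Although the study is powered to detect a significant difference between groups" and confines its sample-size caveat to rare adverse events and subgroup analysis. The Background section of the Introduction contrasts the trial with earlier studies as "employing a randomized, double-blind, placebo-controlled design with an adequately powered sample size".

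Sample Size and Power Calculations starts from a 28-patient pilot in which "80% of the participants treated with PRP experienced an improvement in their symptoms". It assumes a 30% difference from saline at 12 months, α of 5% and power of 80%, reaches 31 per group, allows for 10% loss, and concludes that "a sample size of 34 participants for each group is required or a sample size of 68". It acknowledges that the pilot outcome and this trial's primary outcome differ and that prior data on LS score change with platelet-rich plasma (PRP) are lacking. It then says that "symptom improvement in the pilot study was used as a surrogate to estimate a conservative effect size for this study".

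The Results section says "The study is closed as of September 2024 due to slow recruitment" and "A total of 34 participants were recruited".

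**The concern.** The number recruited is half the number that the article itself says is needed, yet the claim of power stands in the present tense and the shortfall does not appear among the limitations. Because the size caveat there is limited to rare events and subgroups, a reader would take the main comparison to be secure. The planned power was also never a statement about the primary outcome, a physician-rated score from 0 to 12.

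What is at stake is how the primary result is read. The Discussion faults earlier studies for inadequate power and presents this trial as the remedy. If the between-arm difference is not significant, a reader who has been told that the trial is powered could take this as evidence that PRP does not work.

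**Working it through.** **Inputs.** From Sample Size and Power Calculations: 80% with PRP, a difference of 30%, α 5%, power 80%, 31 per group before loss, 10% loss, 68 in total. From Results: 34 recruited. From Randomization and Blinding: 1:1 allocation.

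**Assumptions, not stated in the article.** The 30% is an absolute difference, so p1 = 0.80 and p2 = 0.50. The 34 split 17:17. The sample size section does not give sidedness, so both are shown. The only mention of a one-sided test is in Statistical Analysis, in the sentence on comparing the arms on baseline characteristics.

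**1. Reproducing the planned 31 per group.** With p̄ = 0.65:

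n = [z_α·√(2p̄(1−p̄)) + z_β·√(p1(1−p1) + p2(1−p2))]² / (p1−p2)²

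Here √(2 × 0.65 × 0.35) = 0.6745, √(0.16 + 0.25) = 0.6403 and z_β = 0.8416.

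- One-sided: (1.645 × 0.6745 + 0.8416 × 0.6403)² / 0.09 = 30.2, so 31. This matches.
- Two-sided: (1.960 × 0.6745 + 0.8416 × 0.6403)² / 0.09 = 38.5, so 39.

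Of the variants tried for 80% versus 50% (pooled, unpooled, arcsine, with and without continuity correction), only the one-sided pooled form without correction gives exactly 31. Allowance for loss: 31 × 1.1 = 34.1 and 31 / 0.9 = 34.4. The stated 34 per group is close to both.

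**2. Power for the same effect at the numbers reached.**

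Power = Φ{[0.30·√n − z_α × 0.6745] / 0.6403}

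| n per arm | One-sided 5% | Two-sided 5% |
|---|---|---|
| 31 (planned, after loss) | 81% | 71% |
| 17 (34 recruited) | 58% | 45% |
| 15 (17 × 0.9 = 15.3) | 53% | 40% |

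Example, n = 17 two-sided: (0.30 × 4.123 − 1.960 × 0.6745) / 0.6403 = −0.133, and Φ(−0.133) = 0.447.

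A two-sided Fisher exact test gives 62% at 31 per arm and 32% at 17.

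**3. The primary LS score.** The article gives no target difference or SD, so only standardized differences can be computed. For a two-sided 5% t test (noncentral t), the smallest difference detectable with 80% power is 0.72 SD at 31 per arm, 0.99 SD at 17 and 1.06 SD at 15. At 17 per arm, power is 29% for 0.5 SD and 62% for 0.8 SD.

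**4. Precision at 17 per arm.**

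- Proportions: 95% CI half-width 1.96 × √(0.41/17) = 0.30, as wide as the assumed effect.
- LS score: t(0.975; 32 df) × √(2/17) = 0.70 SD, against 0.51 SD at 31 per arm.

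**5. The word *conservative*.** An effect size is conservative if it is smaller than the one expected on the outcome being tested. The article says that it has no data on PRP's effect on the LS score, so it has nothing to set the surrogate against.

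**The case against.** Much of this is already disclosed. The sample size section says openly that the pilot outcome differs from the primary outcome, the Results report the 34, and both the Abstract and the Results report closure for slow recruitment. The Background wording is partly about design: just before the quoted phrase, the article says that the trial was designed to be adequately powered. The Limitations open by speaking as a protocol about anticipated limitations. All of this stands. It narrows the firm contradiction to the present-tense clause in the Limitations; the Background needs only alignment.

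A reader might infer that power on the planning assumption is simply 45%. The documents do not support a single figure. The 31 per group reproduces as a one-sided calculation, so setting the planned 80% beside a two-sided 45% mixes two bases. Like for like, the fall is from 81% to 58%, or from 71% to 45%.

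A reader might also infer that the investigators plan to read a null result as no effect, or that they hid the mismatch of outcomes. No passage says the first, and the sample size section contradicts the second. The risk of misreading is an inference from the wording.

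What the objection does not rescue is the claim itself. Even the more favourable, one-sided figure is 58%, and the article appeared after recruitment had ended and the final number was known.

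**Conclusion.** The statement in the Limitations that the study is powered is wrong for the trial as it closed, and the section omits the shortfall that makes it wrong. For the article's own planning effect, power with 34 participants is about 45% (two-sided) to 58% (one-sided), or 40% to 53% with 15 per arm after loss. A non-significant result would therefore be about as likely as not even if PRP had the planned effect. At full recruitment, with 31 per arm analysed, 80% holds only one-sided. These figures rest on reading 30% as 80% versus 50% and on a 17:17 split.

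For the primary LS score no planned power exists. At 17 per arm a two-sided test reaches 80% only for a difference of about 1.0 SD, and *conservative* has no support. The finding concerns what the article claims; it does not show a fault in the randomization, the data or the conduct of the trial.

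**What to change.** - **Limitations:** delete the claim that the study is powered. List the shortfall (34 of 68), with power for the planning effect given both ways, about 45% two-sided and 58% one-sided, and with the 50% control rate and the 17:17 split named as assumptions. Replace the assumed split with the actual one.
- **Background:** say that the trial was designed for 68 participants and closed at 34.
- **Sample Size and Power Calculations:** delete *conservative*, and say that the sample size was not derived for the LS score.
- **Reading of the result:** say that the between-arm difference in LS score will be reported with its 95% CI, and that a non-significant result will not be read as evidence of no effect. Analysis was already under way in 2025, so present this as a reporting commitment and do not describe it as prespecified.

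The cost is a few sentences. No data, design feature or procedure changes. The downside is that the trial's claim becomes more modest.

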### Comparison With Prior Work

Previous investigations [20,21] into the use of PRP for vulvar LS have largely consisted of case reports, small cohort studies, and pilot trials, many of which lacked standardization in PRP preparation and outcome measurement. These earlier studies often demonstrated promising symptomatic improvements but were limited by heterogeneity in design, short follow-up durations, and absence of control groups. This protocol addresses several of these gaps by incorporating a parallel-group, double-blind, randomized controlled trial design with standardized PRP preparation, objective clinical scoring, and validated patient-reported outcome measures. By using a clearly defined placebo (saline) control and ensuring long-term follow-up, this study aims to provide robust evidence to inform future clinical practice.

### Conclusions

This protocol outlines a rigorous, placebo-controlled, double-blind randomized controlled trial designed to assess the safety and efficacy of autologous PRP injections for the treatment of vulvar LS. By employing standardized preparation methods, validated clinical and quality of life outcome measures, and long-term follow-up, this study aims to address the methodological limitations of prior research. The findings from this trial have the potential to inform clinical practice by providing high-quality evidence on the role of PRP as an alternative or adjunctive therapy in patients who are unresponsive to standard topical steroid treatment.

## Appendix

Multimedia Appendix 1 Participant information sheet and consent form.

Multimedia Appendix 2 Protocol for platelet-rich plasma preparation and saline preparation.

Multimedia Appendix 3 Participant appointment schedule.

Multimedia Appendix 4 Demographic data collection sheet.

Multimedia Appendix 5 Visual Analogue Scale.

Multimedia Appendix 6 Australian Pelvic Floor Questionnaire.

Multimedia Appendix 7 Dermatology Life Quality Index.

Multimedia Appendix 8 Study recording sheet.

Multimedia Appendix 9 Participant flow diagram.

Multimedia Appendix 10 CONSORT (Consolidated Standards of Reporting Trials) checklist.

Multimedia Appendix 11 SPIRIT (Standard Protocol Items: Recommendations for Interventional Trials) checklist.

## Abbreviations

CONSORT: Consolidated Standards of Reporting Trials
LS: lichen sclerosus
PRP: platelet-rich plasma
